### Sample size

The 2010–2011 data from the ICU of the Dhaka Hospital of the icddr, b (the proposed study site) revealed that among the 36 severely malnourished children with shock, 22 died, that is, mortality rate among SAM children with septic shock was 61% (22/36). We assumed that the proposed interventions would reduce the case fatality rate by 50%, that is, the rate will decrease from 61% to 31%.

To detect this magnitude of difference in the death rate, with 80% power (20% type II error) and 0.05 type I error, the required sample size is 40 children in each of the three groups. Considering around 10% drop-outs after enrolment, the total sample size would be 45 children at least in each of the three groups, that is, a total of 135 children—the final sample size of our study.

### Data collection, management and analysis

Data will be collected using a hard copy structured case record form. Data will be entered into a personal computer on the online platform named Research Electronic Data Capture. The data management team will check the consistency of data and will download and store the dataset as a backup to ensure data security. Statistical analyses will include descriptive as well as analytical methods. The effect of the intervention will be assessed by performing an intention-to-treat analysis as well as a per-protocol analysis. We anticipate that there will be no differences in the sociodemographic data among the three groups. Categorical variables will be compared using the χ^2^ test or Fisher’s exact test as appropriate. When the variables of interest are continuous and distributed normally, the statistical significance of group means will be evaluated by analysis of variance. When the variables are continuous and not normally distributed, the statistical significance of group differences will be determined by the Kruskal-Wallis test. The post hoc test will be done if required. To determine the differences in primary outcome, that is, case fatality among groups, we will perform the χ^2^ test or Fisher’s exact test as appropriate. The multiple generalised linear model (log-binomial regression) will be performed to explore the effect of interventions on case fatality after adjusting for potential confounders, including the child’s age, child’s sex, child’s morbidity status, wealth status, etc. The strength of the differences will be determined by calculating the relative risks with 95% CIs. In addition, we will analyse the Kaplan-Meier survival curve to compare the survival times among the three treatment groups. A p<0.05 will be considered statistically significant. The scheduled interim analysis will be done after 50% of enrolment or earlier if the data safety and monitoring board (DSMB) advises. DSMB is an independent body, they review and follow the entire study and provide time-to-time suggestions. We will follow the stopping rule if the p<0.003, as recommended by Pato and Fleming.^21^ Data analysis will be done using SPSS for Windows (V.20.0., IBM and Epi Info (V.7.0, USD, Stone Mountain, Georgia, USA) or STATA (V.15.0 SE).

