### Laboratory testing and sample handling

We are performing laboratory tests after the enrolment of a child in the study that includes blood for haemoglobin percentage, total and differential counts of white cell count (WCC), haematocrit, blood culture and antimicrobial susceptibility of pathogens, serum electrolytes and creatinine, calcium and magnesium, serum bilirubin, serum lactate, C reactive protein, procalcitonin and cardiac troponin I, stool (rectal swab for cholera, Salmonella, Shigella and Campylobacter) and urine culture, chest radiograph, and arterial or capillary blood gas analysis. We are also doing a test for the exclusion of dengue during the dengue prevalent period in the country. We are checking serum lactate at enrolment and 4–6 hours after enrolment. Our target is to send samples for laboratory tests within 30 min to 1 hour of enrolment. When a child is in shock, very often it is difficult to get an adequate amount of blood for proposed testing. Then we prioritise tests based on clinical relevance. We are doing the blood grouping, screening and cross-matching while we are following a child for study eligibility. We are performing cardiac ultrasonography during screening, enrolment and 4–6 hours later after enrolment. As we are enrolling children 24×7, the study physicians are doing the bedside cardiac ultrasound and storing the images of specific preselected parameters. Later the images are reviewed by experienced cardiologists to get the measurements.

We are archiving blood samples and planning to check serum leptin at the end of the study.

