### Outcome measures

Primary outcome variable is the case fatality rate (at 28±3 days from the day of enrolment). The secondary outcome variables are the rate of treatment failure, rate of MAP stabilisation at 48 hours after enrolment, need for mechanical ventilation, the incidence of heart failure, duration of ICU stay and total hospitalisation, time-to-achieve recovery, evaluation of cardiac function by POC ultrasonogram (right ventricular function, left ventricular function and IVC collapsibility).

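### The ultrasound secondary outcomes have an enrolment scan and a 4–6 hour scan, but the only tests named for continuous outcomes (ANOVA, Kruskal-Wallis) make no baseline adjustment

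*Protocol article*

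**What the plan says.** All references are to the protocol article.

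- **Outcome measures** lists among the secondary outcomes "evaluation of cardiac function by POC ultrasonogram (right ventricular function, left ventricular function and IVC collapsibility". It gives no parameter, time point, or form (value or change).
- **Laboratory testing and sample handling** gives the timing: "We are performing cardiac ultrasonography during screening, enrolment and 4–6 hours later after enrolment". Table 1 puts the enrolment scan in the column before study drug administration, so a pre-treatment value of each parameter should exist.
- **Data collection, management and analysis** sets the method for continuous variables: "When the variables of interest are continuous and distributed normally, the statistical significance of group means will be evaluated by analysis of variance". For non-normal variables, "the statistical significance of group differences will be determined by the Kruskal-Wallis test". Post hoc tests follow if required.
- The same section names one covariate-adjusted model, a log-binomial regression "to explore the effect of interventions on case fatality after adjusting for potential confounders". Its listed covariates (age, sex, morbidity, wealth status and the like) do not include a scan value.

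**The concern.** The trial pays for a scan before treatment and another a few hours after. For an outcome measured at both times, the enrolment value usually explains part of the spread between children in the later value. These children are 1–59 months old and will differ in ventricular function and volume status before any study drug is given. A plain ANOVA or Kruskal-Wallis on the later value leaves that spread in the error term. A plain ANOVA on the change uses the enrolment value, but with a fixed weight of one, which is generally not the best weight.

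What is at stake is the precision of the ultrasound comparison, which the article lists among its strengths. There is a smaller point too. The trial is not masked, and the analysed form (later value or change) is left open, so it should be fixed before the data are examined.

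**Working it through.** **1. The plan's own figure.** The only sizing is for death: 61% versus 31%, "with 80% power (20% type II error) and 0.05 type I error". With unpooled variance and a two-sided test:

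n = (1.960 + 0.842)² × (0.61×0.39 + 0.31×0.69) / 0.30² = 7.849 × 0.4518 / 0.09 = 39.4, so 40 per group.

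Allowing 10% drop-out, 40 / 0.9 = 44.4, so 45 per group and 3 × 45 = 135. The stated figures reproduce. They say nothing about the power of the ultrasound comparisons.

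**2. Inputs for the ultrasound outcomes.**
- From the article: three equal arms and the significance level ("A p<0.05 will be considered statistically significant", taken as two-sided).
- Assumed, because the documents give no value: the correlation r between the enrolment and 4–6 hour values (range 0.3 to 0.7), equal SD at both times, and 80% power for the unadjusted comparison of 4–6 hour values.

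**3. Variance under each analysis**, in units of the variance of the 4–6 hour value:
- 4–6 hour value alone: 1
- change from enrolment: 2(1 − r)
- ANCOVA: 1 − r²

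ANCOVA is never worse on variance. Against the later value, 1 − (1 − r²) = r² ≥ 0. Against the change, 2(1 − r) − (1 − r²) = (1 − r)² ≥ 0. Its cost is one error degree of freedom (for example 117 to 116 with 40 per arm).

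**4. Pairwise power.** An 80% start means (difference/SD) × √(n/2) = 1.960 + 0.842 = 2.802, which is 0.63 SD at 40 per arm or 0.59 SD at 45. Power is Φ(2.802/√v − 1.960), where v is the variance from step 3. For ANCOVA at r = 0.5, v = 0.75 and 2.802/0.866 − 1.960 = 1.275, giving 89.9%.

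**5. Three-arm F test.** The noncentrality that gives 80% (9.886 at 40 per arm) is divided by 1 − r², and one error degree of freedom is removed.

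| r | 4–6 h value | Change | ANCOVA, pairwise | ANCOVA, three-arm F |
|---|---|---|---|---|
| 0.3 | 80% | 65.8% | 83.6% | 83.8% |
| 0.5 | 80% | 80.0% | 89.9% | 90.4% |
| 0.7 | 80% | 95.1% | 97.5% | 98.0% |

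The gain over the 4–6 hour value runs from about 4 points (r = 0.3) to about 18 (r = 0.7). The pairwise gain over the change score runs the other way: 17.8 points at r = 0.3, 9.9 at 0.5 and 2.4 at 0.7.

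**6. Sensitivity to the starting power.** At r = 0.5 the pairwise gain is about 12 points from a start of 50%, 60% or 70%, 10 from 80%, and 6 from 90%.

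**7. Fewer usable scans.** If only 30 children per arm (an illustration) had a 4–6 hour scan, a 0.59 SD difference would have 62.8% power unadjusted and 75.2% with ANCOVA at r = 0.5.

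**The case against.** The strongest objection is that this is a journal article condensing a longer protocol. The covariates for one family of secondary outcomes are the kind of detail left to the full protocol or analysis plan, and ANOVA in a randomised trial is a valid test. Part of this stands: nothing here is invalid, and an unseen plan may already adjust. But the article does not simply stay silent. It assigns a method to continuous variables in general and names adjustment for death only, so the comment is on a stated method.

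Four stronger readings are tempting, and the documents do not support them.

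- **That the enrolment scan is thrown away.** The analysis section does not define the analysed variable. If it is the change, the enrolment scan is used, though still less efficiently than by ANCOVA.
- **That a fixed amount of power, such as 10 points, is lost.** That figure needs r = 0.5 and an 80% start. The article's 80% belongs to the death comparison.
- **That chance imbalance at enrolment biases the unadjusted test.** Under randomisation it is already part of the unadjusted standard error and of the 5% error rate. Adjustment improves precision; it does not repair a bias.
- **That 40 children per arm will have evaluable scans.** That number comes from the mortality calculation. Early deaths may reduce it, and Table 1 shows no fixed 4–6 hour scan: it marks scans under rescue therapy and, only where needed, during the hospital course.

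**Conclusion.** The concern holds as an efficiency point on secondary outcomes. The protocol article names no baseline-adjusted analysis for the ultrasound measures, although it schedules an enrolment scan that would support one. Whichever variable was meant, ANCOVA is at least as efficient apart from one degree of freedom. The size cannot be fixed from the documents. It is about 4 to 18 points if r lies between 0.3 and 0.7 and the unadjusted comparison of 4–6 hour values has 80% power, and it changes with both assumptions. The case-fatality analysis and the 135-child sample size are not touched.

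**What to change.** Add to the analysis section that, for right and left ventricular function and IVC collapsibility, the 4–6 hour value will be analysed by ANCOVA on treatment arm and the enrolment-scan value of the same parameter. Report adjusted differences of dopamine versus blood and epinephrine versus blood with 95% confidence intervals. For a clearly non-normal parameter, use a log transform (the difference then reads as a ratio) or rank ANCOVA in place of Kruskal-Wallis. Rank ANCOVA gives a test but no difference on the original scale.

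Three conditions go with it:

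- Do not substitute the screening scan when the enrolment image is unusable. The study procedure section has children receiving fluid boluses during screening, so a screening scan may precede volume loading, which bears directly on IVC collapsibility.
- Report how many children per arm have a usable 4–6 hour scan, and why the others do not. ANCOVA does not solve scans missing through early death.
- Reconcile the fixed 4–6 hour scan in the laboratory section with Table 1, so that it is clear whether every child is due that scan.

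The cost is a few lines of text and one degree of freedom per model, with no new scans or data collection. The wording should be settled before the ultrasound data are compared by arm.

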#### Recovery time

Time required for the restoration of MAP after starting the intervention for shock.

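### ICU stay, hospital stay and time to recovery fall under ANOVA or Kruskal-Wallis although death truncates all three; if deaths precede discharge, the higher-mortality arm can appear to have the shorter stay

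*Protocol article*

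**What the plan says.** Outcome measures lists among the secondary outcomes "duration of ICU stay and total hospitalisation, time-to-achieve recovery". Recovery time is defined as "Time required for the restoration of MAP after starting the intervention for shock".

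Data collection, management and analysis gives one rule for continuous variables. Normally distributed ones go to ANOVA; otherwise, "When the variables are continuous and not normally distributed, the statistical significance of group differences will be determined by the Kruskal-Wallis test". Kaplan-Meier is named, but only for survival. The same section promises an intention-to-treat analysis alongside a per-protocol one. It does not pair tests with outcomes by name, and it does not say how a child who dies before discharge or before MAP is restored enters these comparisons.

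Sample size starts from 22 deaths among 36 children and assumes that "the rate will decrease from 61% to 31" per cent. Nutritional rehabilitation says that, once the acute illness is over, caregivers are asked to remain with the child in the rehabilitation unit for 2–3 weeks.

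**The concern.** ANOVA and Kruskal-Wallis need one number per child and read a smaller number as a shorter duration. Death spoils that reading in two ways.

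- **ICU and hospital stay.** Death ends the stay. A child who dies on day 1 and is counted at the observed stay ranks among the best results. With unequal mortality, this pulls down the stay in the arm with more deaths.
- **Time to recovery.** A child who dies with MAP never restored has no value and leaves the comparison. Those who remain are selected by what happened after randomisation.

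If the trial succeeds as assumed, the stay outcomes could reach p<0.05 in favour of the arm with twice the mortality and appear to contradict the primary result.

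**Working it through.** **Inputs from the protocol.** Fatality is 61% (taken here as the blood arm) and 31% (each drug arm), with 80% power and type I error 0.05. Sidedness is not stated; two-sided is assumed.

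**The plan's own figure.** Unpooled two-proportion formula: (1.960 + 0.842)² × (0.61×0.39 + 0.31×0.69) / 0.30² = 39.4, so 40 per arm. Then 40/0.90 = 44.4, so 45 per arm and 135 in total. This agrees with the protocol.

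**Expected deaths.** 45 × 0.61 = 27.5 in the blood arm and 45 × 0.31 = 14.0 in each drug arm. Overall fatality is (0.61 + 0.31 + 0.31)/3 = 41%.

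**Direction of the effect on mean stay.** Let survivors stay S days and deaths occur at D days, the same in every arm. Mean stay is (1 − p)S + pD, so the drug arms exceed the blood arm by (0.61 − 0.31)(S − D) = 0.30(S − D). With S = 10 and D = 2 (assumed):
- blood arm: 0.39×10 + 0.61×2 = 5.12 days
- drug arm: 0.69×10 + 0.31×2 = 7.52 days

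The lower-mortality arms look 2.4 days worse. The sign is that of S − D: zero when deaths come as late as discharge, reversed when they come later.

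**Three-arm simulation of stay.** 45 per arm, fatality 61/31/31%, survivor stay identical in all arms, deaths counted at observed stay. Times are lognormal (log-SD 0.6 for survivors, 0.9 for deaths), with 2,000 trials per row. All times are assumptions.

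| Survivor median (d) | Death median (d) | Median stay, blood arm | Median stay, drug arms | Kruskal-Wallis p<0.05 | Blood arm has shortest median |
|---|---|---|---|---|---|
| 14 | 1 | 2.3 | 9.8, 9.9 | 72% | 99% |
| 14 | 2 | 4.4 | 10.1, 10.2 | 63% | 98% |
| 14 | 4 | 7.2 | 10.9, 10.9 | 46% | 92% |
| 14 | 7 | 9.8 | 12.0, 12.1 | 19% | 76% |
| 14 | 14 | 14.1 | 14.0, 14.0 | 4% | 33% |
| 7 | 1 | 2.2 | 5.0, 5.1 | 64% | 98% |
| 7 | 2 | 3.6 | 5.4, 5.4 | 46% | 91% |
| 7 | 4 | 5.2 | 6.2, 6.2 | 16% | 66% |
| 7 | 7 | 7.0 | 6.9, 7.0 | 5% | 34% |
| 7 | 14 | 10.0 | 8.2, 8.2 | 21% | 6% |

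ANOVA on log stay behaves almost identically (63% in the 14/2 row). With equal fatality of 45% in all arms (survivor median 10 days, death median 2), rejection is 6%, so differential mortality produces the effect.

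**Survivors only.** With survivor median 10 days in every arm, rejection is 5% and the medians agree. The shortening has gone, but only because this model makes a survivor's stay unrelated to the risk of death.

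**Time to recovery.** Underlying recovery is identical in all arms (median about 6 hours, assumed) and every child who dies is dropped; 4,000 trials per setting.
- No link between severity and death: medians 6.1 hours in all arms, rejection 5%.
- Increasingly strong links: blood arm against drug arms 4.7 v 5.3, 4.3 v 5.0 and 3.9 v 4.9 hours, rejection 7%, 12% and 17%.

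Dropping every death overstates this bias, because some children will die after MAP was restored and do have a value.

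**The case against.** The general rule is standard wording that also covers baseline variables. It does not name these outcomes or say that deaths enter at their observed stay. Which children are analysed and how deaths are scored may be settled in an analysis plan that is not shown. That is fair as regards the scoring of deaths, and silence on it is not the point made here. What stands is that the tests themselves are fixed in this document, no other method is given for these outcomes, and neither natural way of applying them works. Counting deaths at observed stay distorts the comparison, and restricting to survivors compares subsets selected after randomisation.

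A reader might infer that the direction is certain, or that all three outcomes must favour the more lethal arm. The documents support neither. They give no stay or death times. For ICU stay, late deaths are plausible, since the protocol provides for mechanical ventilation and escalating rescue therapy, and the direction then reverses. Time to recovery has no mechanical shortening at all.

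The consequences are also bounded. The outcomes are secondary, mortality will be reported beside them, and treatment failure and MAP stabilisation at 48 hours give rate measures of early haemodynamic response.

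**Conclusion.** The concern holds in a conditional form: the stated tests do not suit three outcomes that death truncates at the fatality the plan assumes.

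- **Total hospitalisation** is most exposed. The rehabilitation stay of 2–3 weeks makes it likely that deaths in acute shock come well before survivors leave. With survivor median 14 days and death median 1 to 4 days, 46–72% of trials show a significant difference produced by mortality alone, nearly always with the shortest median in the higher-mortality arm.
- **ICU stay** is exposed if deaths are early. The effect disappears when deaths come as late as ICU discharge and reverses when they come later.
- **Time to recovery** has a separate, smaller bias (7–17% rejection), present only if severity drives both death and slow recovery.

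These sizes rest on assumed times and on the planned 61% v 31% fatality being realised. The sample size and the primary comparison are unaffected. The change should be made, but the trial's main conclusion does not depend on it.

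**What to change.** In Data collection, management and analysis, take these three outcomes out of the ANOVA/Kruskal-Wallis rule. Analyse ICU discharge alive, hospital discharge alive and MAP restoration as time-to-event outcomes, by cumulative incidence with death as a competing event, including every randomised child. State how referral and leaving against medical advice are handled, since both also end a stay. Report stay among survivors by arm as descriptive only, without a test.

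ICU-free days to day 28 with death ranked worst may be added as a supportive analysis, provided the text says that it mainly reflects mortality: with identical survivor stays (median 10 days), ranking deaths worst gives p<0.05 in 75% of simulated trials. The discharge-alive curves carry mortality too. If every survivor is eventually discharged, they level off at 1 − 0.61 = 39% and 1 − 0.31 = 69%, which is why survivor stay should stand beside them.

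**Cost.** No new data: stays, recovery time and deaths are already recorded, and the planned Kaplan-Meier analysis needs death times anyway. The price is slightly more analysis work and a less familiar summary than a mean or median stay. Because the trial is not masked and recruitment is under way (18 enrolled by August 2022), date the change and make it before any comparison by arm.

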#### Reporting of adverse events

Serious adverse events (deaths) after initiation of the study intervention are recorded and presented to the DSMB within 24 hours of the event. The report includes a detailed clinical history, the study intervention and management given until the outcome. We contacted over the phone for study participants who were referred.

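### The only numerical stopping rule, an undirected p<0.003 at about 22 children per arm, gives almost no formal protection against a harmful drug at the plan's assumed 61% blood-arm mortality

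*Protocol article*

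**What the plan says.** All references are to the protocol article.

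- **Timing** (Data collection, management and analysis): "The scheduled interim analysis will be done after 50% of enrolment or earlier if the data safety and monitoring board (DSMB) advises".
- **Criterion** (same section): "We will follow the stopping rule if the p<0.003". No direction is given, there is no separate limit for harm, and it is not said whether the test is each drug against blood or one three-arm test. The test named for case fatality is chi-square or Fisher's exact.
- **Size and mortality** (Sample size): "a total of 135 children—the final sample size of our study", which is 45 per arm. The baseline rate is "mortality rate among SAM children with septic shock was 61% (22/36").
- **Comparator** (Study intervention and procedure): both drugs are compared with blood, the WHO standard.
- **Deaths**: "Serious adverse events (deaths) after initiation of the study intervention are recorded and presented to the DSMB within 24 hours of the event" (Reporting of adverse events). Each report names the study intervention. The Ethics section says that the DSMB's recommendations will be followed.

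**The concern.** A strict symmetric threshold at an early look is a common choice for stopping for benefit. Here the same number is the only one available for harm, and the starting mortality is high. From 61% a drug can fall a long way but can rise by at most 39 percentage points, and 22 children per arm is too few for most of that rise to reach p<0.003.

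Two of every three children are allocated to drugs whose early use in severely malnourished children with this condition has, according to the Introduction, never been studied. If one of them raises mortality, the stated rule is very unlikely to detect it at the only scheduled look.

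**Working it through.** **1. The plan's own figure.** Inputs from Sample size: 61% v 31%, 80% power, 0.05 type I error (two-sided assumed).

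n = (1.96 + 0.842)² × (0.61×0.39 + 0.31×0.69) / 0.30² = 39.4, so 40 per arm. Then 40 / 0.9 = 44.4, so 45 per arm and 135 in total. The stated size reproduces.

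**2. Size at the look.** 135 / 2 = 67.5 children, so 22 to 23 per arm. At 61%, 22 × 0.61 = 13.4 blood deaths, so 13 or 14 is typical.

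**3. Deaths needed to cross towards harm.** Take 0.003 as two-sided (|z| about 2.97). For b blood deaths and d drug deaths of n each:

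z = [(d − b)/n] / √[2p̄(1 − p̄)/n], with p̄ = (b + d)/(2n).

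- b = 13, d = 22, n = 22: p̄ = 35/44 = 0.795; z = 0.409 / 0.1216 = 3.36, p = 0.0008. Crosses.
- b = 13, d = 21: p̄ = 34/44 = 0.773; z = 0.364 / 0.1264 = 2.88, p = 0.0040. Does not cross.

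All tables were enumerated with both tests:

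| Blood deaths | Smallest drug-arm count, chi-square | Fisher |
|---|---|---|
| 11/22 | 20 | 21 |
| 12/22 | 21 | 22 |
| 13/22 | 22 (p = 0.0008) | 22 (p = 0.0014) |
| 14/22 | 22 (p = 0.0018) | none (22/22 gives p = 0.0036) |
| 15/22 | none | none |

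At 23 per arm with 14 blood deaths, both tests need 23/23.

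**4. An earlier look.** At 20 per arm with 12 blood deaths, 20/20 gives Fisher p = 0.0033, so Fisher cannot cross. The same threshold with fewer children is stricter.

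**5. A three-arm test instead.** With the other drug also at 13/22, 22/22 is still needed (p = 0.0021; 21/22 gives 0.0088). If the other drug has 7/22 deaths, about its planned rate, 19/22 crosses (p = 0.0011), but that result is driven by the contrast between the two drugs and not by harm against blood.

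**6. Probability of crossing towards harm.** Sum Bin(b; 22, p_blood) × Bin(d; 22, p_drug) over all tables that cross with d > b. The last two columns apply one-sided p<0.05 against the drug at the same look. All cells are chi-square / Fisher.

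| True mortality, blood v drug | Stated rule | One-sided 0.05 guideline |
|---|---|---|
| 61% v 61% | 0.2% / 0.1% | 5% / 2% (false alert) |
| 61% v 75% | 2% / 1% | 27% / 16% |
| 61% v 80% | 5% / 3% | 42% / 28% |
| 61% v 90% | 22% / 13% | 77% / 64% |
| 31% v 61% | 18% / 11% | 64% / 52% |

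Against 13/22 blood deaths the guideline is reached at 18/22 (chi-square) or 19/22 (Fisher).

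**7. Cost in false alerts.** With both drugs equal to blood at 61%, simulation by chi-square gives about 9% for an alert on either drug at one look. Testing at 10, 20, 30 and 40 per arm raises this to about 20%.

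**8. Deaths before the look.** At 68 children: (68/3) × (0.61 + 0.31 + 0.31) = 27.9 under the planned effect, or 68 × 0.61 = 41.5 with no effect.

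**The case against.** A reader might infer that a harmful arm would run to full enrolment because the rule cannot work for harm. The documents do not support that. The trial is not masked, each death report names the intervention, and blocked allocation keeps arm sizes similar, so the DSMB could keep a running tally. It may ask for an earlier look, it comments from time to time, and its recommendations are followed. Nothing says that it may recommend stopping only at p<0.003. Nor is crossing impossible: if few children on blood have died, or the drug is very harmful, the rule can be met.

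Three further points deserve weight. First, the article never says that the threshold covers harm. It may be meant for benefit, with harm left to DSMB judgement and any guideline placed in a charter or in full protocol version 2.2, neither of which is shown. Second, any strict early limit is insensitive: for benefit at the planned 61% v 31% the crossing probability is also only 18% / 11%. Third, the drug-arm rates of 75% to 90% are mine. The highest fatality that the article cites is 69%, and at 61% v 69% even the one-sided guideline would alert only 14% / 7% of the time.

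What remains is narrower. The article states one rule without direction, and on its own mortality figure that rule hardly responds to harm. Insensitivity is usual and often wanted when stopping early for benefit; it is less acceptable when the question is excess deaths. Single case reports amid an expected 28 to 41 deaths are a weak signal when no comparison by arm is stated.

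**Conclusion.** The concern holds for the formal rule and no further. At 61% blood-arm mortality and 22 children per arm, p<0.003 gives almost no formal protection against a harmful drug: 22/22 deaths are needed against 13/22, and the chance of crossing is 5% / 3% at a true 80% and 22% / 13% at 90%. Informal stopping by the DSMB remains open, so it should not be concluded that a harmful arm would necessarily continue.

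This rests on a two-sided 0.003, each drug tested against blood, blood mortality near 61%, and drug-arm rates that I assumed. The limit eases to 20/22 or 21/22 if chance leaves 11/22 deaths on blood. A change is worth making because it is cheap and concerns patient safety.

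**What to change.** 1. State that p<0.003 applies to stopping for benefit.
2. Add a non-binding harm guideline on mortality for each drug against blood at the scheduled look, for example one-sided p<0.05 against the drug, which prompts DSMB review. Name the test, since chi-square and Fisher differ materially (42% v 28% alert at 61% v 80%).
3. Give the DSMB closed tables of deaths and numbers randomised by arm at fixed intervals, for example every 30 children or every 6 months, whichever comes first, without a formal test at each.

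The cost is protocol and DSMB charter wording and short tables from data already collected. The downside is a false alert of about 5% / 2% per drug at the one look, or about 9% for either drug by chi-square. Testing every 30 children would raise that to about 20%, which is why the interval tables should be descriptive. The DSMB may override an alert, and a non-binding harm guideline does not inflate the type I error for benefit.
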